### Patient enrollment and randomization

Sixty patients with NSTE-ACS (includes unstable angina pectoris and non-ST segment elevation myocardial infarction) from three centers in Huaihai economic zone (Supplementary Table S1) will be enrolled in this trial. The main inclusion and exclusion criteria are listed in Tables 1, 2, respectively.

**Table 1 tab1:** Inclusion criteria.

1. Male or non-pregnant female aged 18–80 years.
2. Clinical diagnosis of acute non-ST segment elevation myocardial infarction.
3. *De novo* coronary artery lesions. Multiple target lesions should be located in different epicardial vessels.
4. Each target lesion should have a length ≤ 40 mm, and diameter between 2.5–4.5 mm by visual assessment.
5. Target lesion with ≥70% diameter stenosis or ≥ 50% diameter stenosis with myocardial ischemia evident by functional assessment.
6. Each patient is allowed to undergo a maximum of three stent implantations, if necessary (except for bailout stent implantation), each target lesion is allowed to be stented with a maximum of two stents.
7. The coronary anatomy is amenable to PCI.
8. Ability to understand the trial purpose, sign informed consent, and have good compliance with medications.

PCI, percutaneous coronary intervention.

**Table 2 tab2:** Exclusion criteria.

1. Acute ST segment elevation myocardial infarction within the past 1 month.
2. Chronic total occlusive lesion, severe left main stem stenosis, lesions with length > 40 mm, bifurcation lesion requiring double stenting, target vessel diameter > 4.5 mm, and vessels unsuitable for OCT imaging such as severely tortuous vessels and vessels with severe dissection, current infection or any active inflammatory diseases.
3. Non interpretable OCT images.
4. Severe calcific lesions that require treatment with debulking techniques.
5. In stent restenosis lesions.
6. Hemodynamic instability such as cardiogenic shock, or left ventricular ejection fraction <40% (by echocardiography or left ventriculography).
7. Renal impairment: eGFR < 60 ml/(min·1.73 m^2^) or serum creatinine>2.5 mg/dL (178 μmol/L), or patients on hemodialysis.
8. Bleeding tendency, history of active peptic ulcer, history of cerebral hemorrhage or subretinal hemorrhage, history of stroke within the past half year, or contraindications for antiplatelet or anticoagulant treatment.
9. Allergy to antithrombotic medications, contrast agent, or Cobalt Chromium.
10. Life expectancy less than 12 months.

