### Treatment and follow-up procedures

In the OCT-guided group, OCT imaging will be performed before PCI to appropriately size stent implantation and following stenting to assess the final results and guide further optimization if needed. A final run will be performed at the end of the procedure to confirm optimal results and exclude common causes of stent failure reported in the literature (17). Patients will be given DAPT (oral aspirin 100 mg once daily, clopidogrel 75 mg once daily, or ticagrelor 90 mg twice daily) and will be put on secondary prevention medications according to the recommended ESC guidelines.

Post discharges all patients will have a follow-up appointment or will be contacted by phone at 1 month, 3 months, 6 months, and 1 year. Subjects assigned to O3/A3 arms will undergo coronary angiography and OCT imaging at 3 months, while those assigned to A6 arm will have invasive assessment and OCT imaging at 6 months after the index procedure (Figure 1). The schedule of enrolment, interventions, and assessments is outlined in Figure 2. The data of each center will be summarized and checked by an independent data monitoring committee.

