### QCA and OCT data acquisition and analysis

Intracoronary nitrate will be administered prior to diagnostic angiography in all the recruited patients unless contraindicated due to low blood pressure. Antithrombotic therapy will be administered according to the local protocol prior to insertion of a guidewire in the coronary arteries.

In the angiography-guided group, stent implantation will be performed and optimized with angiography guidance according to local standard practice based on operator’s visual assessment (stent to artery ratio, 1:1). At the end of the procedure, an OCT examination will be performed for research purposes. The collected images will not be available to the operators and these images will be stored and transferred to a dedicated core-lab for image analysis.

In the OCT-guided groups, PCI will be performed under OCT guidance according ILUMIEN III: OPTIMIZE PCI algorithm. The overall procedural approach for OCT-guided stent implantation and post-implant optimization also follows this algorithm (18). In short, the stent size is chosen based on OCT measurement, and post-dilation performed under OCT guidance to achieve fully stent struts apposition and satisfactory stent area (19).

Optical coherence tomography images will be acquired in the culprit vessel and non-culprit vessels using a commercially available C7 or OPTIS imaging system (Abbott, Santa Clara, United States). The imaging catheter will be advanced at least 10 mm distally to the culprit lesion and will be pulled-back using an automated pull-back device under contrast media injection for blood clearance. A second pull-back will be performed in case of long lesions so as the catheter to cover the entire segment of interest.

Repeat coronary angiography and OCT imaging will be also performed at 3- or 6-month follow-up according to the study protocol. The angiographic and OCT imaging data collected at baseline and follow-up will be anonymized and transferred to an independent core laboratory for further analysis.

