### Study endpoints

The primary endpoint of the study is the incidence of stent strut coverage (%) at 3- or 6-month follow-up.

The secondary endpoints of the study include angiographic, OCT, and clinical and biomarker outcomes that are listed in Table 3.

**Table 3 tab3:** Endpoints of the trial.

Primary endpoint
The degree of stent struts neointimal coverage (%) at 3 and 6 months
Secondary endpoint
OCT endpoint: Assessed at 3 and 6 months
1. Average and minimal stent diameter, area, and volume.
2. Average and minimal lumen diameter, area, and volume.
3. Average and minimal strut coverage thickness.
4. Strut malposition rate.
5. Vascular repair index.
Clinical endpoints: Assessed at 1, 3, 6, and 12 months
1. Major adverse cardiac events (MACE) composite of cardiac death, target vessel myocardial infarction (TV-MI), and clinical ischemia-driven revascularization.
2. Cardiac death.
3. Non-fatal MI.
4. All revascularization.
5. Target lesion revascularization.
6. Target vessel revascularization.
7. ARC-defined stent thrombosis (early, late, very-late, definite, probable, and possible stent thrombosis).
Molecular biology endpoints: Assessed at baseline, 3 and 6 months
1. Lipid levels (total cholesterol, low-density lipoprotein, high-density lipoprotein, ratio of low-density lipoprotein to high-density lipoprotein, and triglyceride).
2. Molecule indicators (hs-CRP, PTX-3, VCAM-1, and MMP-9).

ARC, academic research consortium; hs-CRP, high sensitive C-reactive protein; PTX-3, pentraxin-3; VCAM-1, vascular cell adhesion molecule-1; and MMP-9, matrix metalloprotein-9.

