Continuous variables will be described as means and SDs if they are normally distributed or median and interquartile range in the case of asymmetric data distribution. Categorical variables will be presented as numbers and percentages. Comparisons of numerical variables are conducted with the Student’s *t* test or Mann–Whitney’ *U* test as appropriate, categorical variables and outcomes were compared by using the chi-squared test or Fisher exact test. A statistical package (SPSS 21.0) will be used for analysis. Two-tailed *p* < 0.05 will be considered statistically significant.

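### Stent and lumen dimensions are to be compared with unadjusted t or Mann–Whitney tests; adjusting for pre-PCI vessel size measured on the baseline angiograms would be a cheap gain in precision, of a size the plan does not let us fix.

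*Protocol article*

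**What the plan says.** Under Statistical considerations, the article gives one rule for all numerical variables: "Comparisons of numerical variables are conducted with the Student’s *t* test or Mann–Whitney’ *U* test as appropriate". It names no covariate, transformation or normalisation to vessel size, and sets two-sided significance at 0.05.

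Table 3 (Study endpoints) lists among the secondary OCT endpoints "Average and minimal stent diameter, area, and volume" and "Average and minimal lumen diameter, area, and volume". These are absolute sizes.

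Table 1 sets the permitted anatomy: "Each target lesion should have a length ≤ 40 mm, and diameter between 2.5–4.5 mm by visual assessment". It also states that "each target lesion is allowed to be stented with a maximum of two stents", so stented length can differ between patients.

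Imaging before stenting differs by arm. In the OCT-guided arm, "OCT imaging will be performed before PCI to appropriately size stent implantation" (Treatment and follow-up procedures). In the angiography-guided arms the article describes OCT only after stenting: "At the end of the procedure, an OCT examination will be performed for research purposes". Baseline angiography is common to all arms: "The angiographic and OCT imaging data collected at baseline and follow-up will be anonymized and transferred to an independent core laboratory". QCA is expanded in the legend of the schedule figure.

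**The concern.** OCT guidance is meant to work partly by achieving an adequate stent area, so the stent and lumen dimensions test the mechanism behind the coverage hypotheses. Absolute stent size also depends on the size of the artery, and volume depends in addition on length. A test that ignores both leaves this anatomical variation in the error term. With 16 to 20 patients per arm, a real gain from guidance could easily be missed, although a covariate measurable before guidance acts could remove part of that variation.

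**Working it through.** **The plan's own figures.** A 24 mm stent read every 0.4 mm gives 24/0.4 = 60 cross-sections, and 60 × 7.9 = 474 struts per patient. Then 7,305/474 = 15.4, rounded up to 16 patients, and 16/0.8 = 20 with 20% drop-out. The three strut counts in Table 4 (6,781, 7,305 and 3,912) also reproduce exactly. All of these concern strut coverage. No effect size, SD or power is stated for stent or lumen dimensions, so everything below rests on assumed variability.

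**Range of anatomy.** Area scales with diameter squared, so the eligibility limits allow a ratio of (4.5/2.5)² = 3.24 in the area of a fully expanded stent. This is a limit, not a distribution.

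**Power formula.** On the log scale, with n per arm and two-sided 0.05, the noncentrality is (ln 1.15 / SD) × √(n/2), for an assumed 15% gain in area. The unadjusted SD is the total SD; the adjusted SD is total SD × √(1 − R²). At n = 16, √(n/2) = 2.83 and ln 1.15 = 0.140.

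**Worked case.** Take a diameter SD of about 0.30 mm (vessel-related SD of log area 0.197) and a residual SD of 0.15.
- Total SD = √(0.197² + 0.15²) = 0.248, and R² = 0.197²/0.248² = 0.63.
- Unadjusted: 0.140/0.248 × 2.83 = 1.60, power 34%.
- Adjusted, covariate without error: 0.140/0.15 × 2.83 = 2.64, power 72%.
- Adjusted, 10% measurement error in diameter: R² falls to 0.31, SD = 0.248 × √0.69 = 0.206, noncentrality 1.92, power 46%.

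The same calculation for three assumed diameter distributions, residual SD 0.15, n = 16. The last column is (adjusted − unadjusted)/adjusted.

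| Diameter | Covariate | R² | Unadjusted | Adjusted | Share of adjusted power lost |
|---|---|---|---|---|---|
| Uniform 2.5–4.5 mm | exact | 0.83 | 18% | 72% | 75% |
| Uniform 2.5–4.5 mm | 10% error | 0.62 | 18% | 39% | 54% |
| Mean 3.2, SD about 0.42 mm | exact | 0.74 | 25% | 72% | 65% |
| Mean 3.2, SD about 0.42 mm | 10% error | 0.46 | 25% | 42% | 40% |
| SD about 0.30 mm | exact | 0.63 | 34% | 72% | 53% |
| SD about 0.30 mm | 10% error | 0.31 | 34% | 46% | 26% |

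**Simulation with absolute QCA error.** The model is log area = log(0.85 × π/4 × d²) + ln(1.15) × arm + normal error with SD 0.12 or 0.18. The covariate is log(d + error), with error SD 0.15 or 0.3 mm. A raw-scale t test is compared with regression on arm and covariate, 16 per arm.
- Diameter centred at 3.1 mm, SD 0.35: about 26–34% unadjusted, 36–71% adjusted.
- Diameter uniform on 2.5–4.5 mm: about 15–19% unadjusted, 33–73% adjusted.

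Mann–Whitney does no better: in a separate set of runs it gave 13–31%, against 15–32% for the raw t test and 30–73% for log-scale ANCOVA. With no true effect, the unadjusted test rejected in 4.2–5.4% of runs, as ANCOVA did.

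**In terms of R² only.** Where the adjusted test has 80% power at n = 16, the unadjusted test has 71%, 58%, 51%, 43% and 24% at R² of 0.2, 0.4, 0.5, 0.6 and 0.8.

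**Volume.** For a 10% gain, residual SD 0.15 and error-free diameter and length (R² 0.86–0.92), power is 8–10% unadjusted and 41% adjusted. Error-free covariates make this a best case for adjustment.

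**The case against.** The strongest reply is that this is a generic paragraph in a condensed article, on secondary endpoints with no stated hypothesis or power, and that adjusted analyses may stand in a full protocol or SAP that is not shown. That limits the weight of the point. It does not remove it, because the article does name the test for these endpoints, and that choice can be judged.

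Several stronger readings are tempting, and the objections to them stand.
- A reader might infer that most of the power is lost. That requires R² above about 0.6, from a wide vessel range or an accurate covariate. For the centred distribution, the unadjusted test kept 48% to 75% of the adjusted power and lost more than half in only one of four cells. The article gives no SD or R², and its eligibility limits do not show how widely enrolled vessels vary.
- A reader might infer that a chance imbalance in vessel size makes the comparison invalid. Vessel size alone can produce an apparent area difference of 15% or more, in roughly 7% of trials (centred) to 24% (uniform) at 16 per arm. Randomisation already accounts for this in the test's error rate, which stayed near 5%. The issue is precision.
- A reader might infer that the covariates are already recorded. Pre-PCI OCT is planned only in the OCT-guided arm, and no text says that reference diameter and lesion length are recorded for everyone. They are measurable from the baseline angiograms.
- A reader might call raw volume confounded by the stent length chosen. That length is a consequence of guidance, and adjusting for lesion length does not remove it. Volume per millimetre would largely repeat average area, which Table 3 already lists.

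It is also fair that an adjusted model must say which lesion supplies the outcome and the covariate when a patient has several. A patient-level unadjusted test needs the same rule.

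**Conclusion.** The point holds as one of efficiency. The stated tests are valid for stent and lumen dimensions but leave vessel size in the error term, and adjustment raised power in every scenario examined. For a 15% area gain with 16 per arm, the range is about 26–34% unadjusted against 36–71% adjusted (centred diameters), or 15–19% against 33–73% (uniform). The effect size, residual CV, QCA error and diameter distributions are all assumptions, so these figures are a range of plausible gains and not a property of this trial. Even adjusted, these endpoints stay below conventional power in all these cells. Nothing here touches the primary endpoint, the three hypotheses or the sample size. It is an inexpensive improvement, not the correction of a wrong figure.

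**What to change.** Pre-specify, before outcome data are seen:
- **Diameter and area (stent and lumen):** ANCOVA of the log value on arm and log pre-PCI QCA reference diameter.
- **Volume:** the same model with log pre-PCI lesion length as a second covariate. Rely on average area, already in Table 3, as the length-free measure of expansion.
- **Covariates:** core-laboratory measurements from the pre-PCI angiogram in all arms. Do not use post-procedure OCT values or implanted stent length, because guidance can affect both.
- **Several target lesions:** state which lesion, or what summary, supplies the outcome and its covariate.
- **Sensitivity analysis:** keep the unadjusted t or Mann–Whitney test.

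The cost is one or two degrees of freedom per model, a few lines of analysis-plan wording, and some QCA measurement on films the core laboratory already receives. No new patients or imaging are needed.

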11. Participation in other clinical trial.
12. Poor compliance, unable to provide written informed consent.
13. Heart transplantation.
14. Undergoing chemotherapy or immunosuppressive therapy.
15. Elective surgery requiring stopping anti-platelet therapy within half a year post stent implantation.
16. Platelet count lower than 100 × 10^9^/L, or more than700 × 10^9^/L, and white blood cell lower than 3 × 10^9^/L, liver diseases (such as hepatitis).

OCT, optical coherence tomography; eGFR, estimated glomerular filtration rate

The recruited patients will be randomized at 1:1:1 ratio to three groups using a computer-generated random sequence table. Patients enrolled in the first group will have OCT-guided revascularization and 3-month follow-up OCT imaging (O3 group, *n* = 20), those in the second group angiography-guided PCI and 3-month follow-up OCT imaging (A3 group, *n* = 20) while the patients recruited in the third group angiography-guided PCI and 6-month follow-up OCT imaging (A6 group, *n* = 20).

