### Blood sample measurement

Blood samples (4–5 mL) will be collected from all subjects prior to the procedure and at 12–24 h after the procedure. Blood samples will be also collected at 3 and 6 months follow up. The samples will be centrifuged at 3,000 r/min for 10 min, and the serum obtained will be isolated and stored at −80°C. Serum levels of total cholesterol (TC), low-density lipoprotein (LDL-C), high-density lipoprotein (HDL-C), and triglyceride (TG) will be measured by automatic biochemical analyzer, the pentraxins 3 (PTX-3), vascular cell adhesion molecule 1 (VCAM-1), and matrix metalloproteinase 9 (MMP-9) by enzyme-linked immunosorbent assay, and the high-sensitivity C-reactive protein (hs-CRP) detected by the immune turbidity method.

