### Statistical considerations

The sample size of this study is based on the previously published literature and the corresponding research hypothesis. This study intends to demonstrate that the incidence of strut coverage in the OCT-guided group is higher than that of angiography-guided group at 3-month follow-up (hypothesis 1). The second hypothesis of this study is that the incidence of stent strut coverage in the OCT-guided group at 3 months is similar to the incidence of strut coverage in the angiography-guided group at 6 months (non-inferiority analysis). If the above hypothesis is confirmed then an additional analysis will be performed that aims to demonstrate that the incidence of covered struts is higher at 3 months in the OCT-guided group compared to the rate of strut coverage noted at 6 months in the angiography-guided PCI (hypothesis 3). In order to control for the type I error, the test significance levels of hypothesis 1 and 2 are set at one-sided 0.025. Since hypothesis 3 is a sequential test carried out on the basis of hypothesis 2, the test significance level is set at one-sided 0.05.

The sample size calculation is based on the assumption that each patient will receive on average 1 stents, and that each stent will have a length of 24 mm. OCT analysis will be performed at 0.4/0.6 mm interval and that 7.9 struts in each cross section will be detected. Based on these assumptions, it is estimated that 474 strut results will be obtained from each patient. We estimate that we will need 7,305 strut estimations in each group to prove with 95% power the primary endpoint of the study. Based on the above assumptions, we estimate that 16 patients should be recruited in each group. Considering a 20% drop-off rate, we estimate that 20 patients should be included in each group (Table 4).

**Table 4 tab4:** Parametric assumptions for hypothesis.

	Experimental group coverage	Control group coverage	Non-inferiority margin	Sample size (stent struts)
Hypothesis 1	93.6%	92%	Not applicable	6,781
Hypothesis 2	95%	95%	1.3%	7,305
Hypothesis 3	96.5%	95%	Not applicable	3,912

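### The biomarker endpoints have a planned pre-procedure sample, but the only stated group comparison is an unadjusted test on an unspecified outcome form; ANCOVA would be more precise at almost no cost

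*Protocol article*

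**What the plan says.** - **Sampling (Blood sample measurement).** Samples "will be collected from all subjects prior to the procedure" and again 12–24 h after it. A separate sentence adds: "Blood samples will be also collected at 3 and 6 months follow up".
- **Endpoints (Study endpoints, Table 3).** The secondary endpoints include "Molecular biology endpoints: Assessed at baseline, 3 and 6 months". They cover lipid levels and hs-CRP, PTX-3, VCAM-1 and MMP-9.
- **Analysis (Statistical considerations).** "Comparisons of numerical variables are conducted with the" Student t test or, as appropriate, the Mann–Whitney U test. A two-tailed p "< 0.05 will be considered statistically significant". No other method for numerical variables is named. Nothing says whether the test is applied to follow-up values or to change from baseline.
- **Size.** Patients are allocated 1:1:1, with 20 enrolled and 16 expected to be evaluable per group.

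**The concern.** The trial pays for a pre-procedure measurement of every marker and lists baseline as one of the assessment times. The stated between-group test then gives that value no defined role. In groups of 16 to 20, two things follow if follow-up values are compared directly:

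- Variation that the pre-procedure value could explain stays in the error term.
- A chance difference between arms at baseline is passed in part into the follow-up difference.

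Because the outcome form is open, follow-up, change and adjusted results could each be presented as the planned analysis. Choosing among them after seeing the data is best prevented in advance.

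**Working it through.** **Inputs from the protocol article.** Struts per patient: 24/0.4 × 7.9 = 474. Patients needed: 7,305/474 = 15.4, so 16 evaluable. With 20% drop-out: 16/0.80 = 20 enrolled. These match the stated figures. They concern strut coverage; no sample size or power is stated for the biomarkers.

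**Assumptions not in the document.** The correlation r between the pre-procedure and follow-up values is taken as 0.3, 0.5 and 0.7. Baseline and follow-up SDs are taken as equal on the analysis scale. Power uses the normal approximation, two-sided 0.05.

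**Residual SD, in units of the follow-up SD**
- Follow-up value alone: 1
- Change from baseline: √(2(1 − r))
- ANCOVA: √(1 − r²)

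**Variance of ANCOVA relative to a test on follow-up values**, 1 − r²: 0.91, 0.75 and 0.51, that is, reductions of 9%, 25% and 51%.

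**Minimum detectable difference at 80% power, 16 per arm**: (1.960 + 0.842) × residual SD × √(2/16) = 0.99 × residual SD.

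| r | Follow-up value | Change | ANCOVA |
|---|---|---|---|
| 0.3 | 0.99 SD | 1.17 SD | 0.94 SD |
| 0.5 | 0.99 SD | 0.99 SD | 0.86 SD |
| 0.7 | 0.99 SD | 0.77 SD | 0.71 SD |

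ANCOVA is the most precise in every row, so the point does not depend on which form the plan intended.

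**Power for an assumed difference of 0.8 SD**
- 16 per arm: 0.62 on follow-up values; 0.66, 0.74 and 0.89 with ANCOVA.
- 20 per arm: 0.72 on follow-up values; 0.76, 0.83 and 0.94 with ANCOVA.

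**Chance baseline imbalance.** The standard error of a baseline difference is √(2/16) = 0.35 SD, or √(2/20) = 0.32 SD. A gap of more than 0.3 SD in either direction has probability of about 40% with 16 per arm and 34% with 20. Only r times the gap is expected to carry into the follow-up difference. For a one-standard-error gap with 16 per arm that is 0.3 × 0.354 = 0.11 SD, 0.5 × 0.354 = 0.18 SD and 0.7 × 0.354 = 0.25 SD.

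**Where the gain disappears.** Estimating one covariate slope from two arms of 16 inflates the variance on average by about 1 + 1/(32 − 4) = 1.036 (normally distributed covariate). At r = 0.2 the net ratio is (1 − 0.04) × 1.036 = 0.99, which is essentially no gain.

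**Optional pooling at 3 months.** Both angiography-guided arms receive the same index treatment and differ in when follow-up OCT is done. Comparing O3 with A3 and A6 combined gives a variance ratio of (1/20 + 1/40)/(2/20) = 0.75, a further 25% reduction if every A6 patient gives a 3-month sample.

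**The case against.** The strongest reply is that the test sentence is generic. It also covers baseline tables and OCT measurements and does not mention the biomarkers. Covariate adjustment of secondary endpoints is often left to an analysis plan, which is not shown here. All three formal hypotheses concern strut coverage, and the Discussion presents the biomarkers mainly as a means to explore associations with neointima and disease progression, not as a contrast between arms. The correlation is unknown: the baseline sample is taken during an acute event and secondary prevention treatment follows, so r may be low.

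Much of this stands, and it limits the point to precision in secondary endpoints. It does not remove it. The article names its tests, they are the only ones given for numerical variables, and the markers are listed as trial endpoints.

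Several stronger readings are tempting but not supported:

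- **That the plan discards the baseline.** The document does not say so. A t test on change would use it, though less efficiently than ANCOVA.
- **That the unadjusted test is invalid.** Randomisation keeps its overall type I error at the nominal level. The loss is in precision, and in bias conditional on the imbalance that happens to occur.
- **That a baseline imbalance passes in full into the result.** Only r times it does.
- **That every patient certainly gives blood at 3 and 6 months.** The wording about all subjects is attached to the samples around the procedure. The follow-up sentence does not repeat it, and follow-up contacts may be by phone. Three-month sampling in A6 is implied, not explicit.

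**Conclusion.** The point holds as a low-priority improvement. The stated comparison is valid, but it leaves the outcome form open and is less precise than an analysis the planned data already allow. The gain ranges from little or nothing below about r = 0.2, through a 9% variance reduction at r = 0.3, to 51% at r = 0.7. It therefore depends on a correlation that the document does not give and that may differ between lipids and acute-phase markers. The other assumptions are equal SDs at the two times, approximate normality on the analysis scale and 16 evaluable patients per arm. Strut coverage, its three hypotheses and the sample size are not affected.

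**What to change.** State that each biomarker at 3 and at 6 months is analysed by ANCOVA on the follow-up value, with arm as factor and the pre-procedure value as covariate. Use the log scale for skewed markers, for outcome and covariate alike. Say explicitly that this replaces the t or Mann–Whitney comparison for these endpoints.

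- Centre is optional as a further covariate. With three centres it costs two degrees of freedom; the baseline value costs one.
- Do not adjust for the 12–24 h sample or the post-procedure OCT findings, because both follow randomised treatment.
- Optionally, add a supplementary 3-month contrast of guidance strategy, O3 against A3 and A6 combined. This requires that A6 patients give a 3-month sample and that the sample is drawn before the 3-month catheterisation; the article states neither. The pooling should not extend to 6 months, because by then A3 has had a repeat invasive procedure and A6 may not have.

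The cost is a few sentences and slightly more analysis work. The main analysis needs no new data; the optional contrast needs the A6 3-month sample confirmed.

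### The primary comparisons are sized on independent struts, and the listed test that fits that unit ignores within-patient correlation; nor do the listed two-tailed tests match the one-sided and non-inferiority hypotheses

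*Protocol article*

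**What the plan says.** Under Study endpoints: "The primary endpoint of the study is the incidence of stent strut coverage (%) at 3- or 6-month follow-up". Table 3 words the same endpoint as a degree of coverage in percent.

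Statistical considerations sets three hypotheses on this endpoint:

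- **Hypothesis 1:** coverage at 3 months is higher with OCT guidance (O3) than with angiography guidance (A3).
- **Hypothesis 2:** 3-month coverage in O3 "is similar to the incidence of strut coverage in the angiography-guided group at 6 months (non-inferiority analysis"), with a 1.3% margin in Table 4.
- **Hypothesis 3:** O3 at 3 months is superior to A6 at 6 months, tested if hypothesis 2 is confirmed.

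On error levels it says that "the test significance levels of hypothesis 1 and 2 are set at one-sided 0.025", and for hypothesis 3 that "the test significance level is set at one-sided 0.05". The sample size is counted in struts per group and then divided by 474 struts per patient to give 16 patients, or 20 after 20% drop-out.

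The last paragraph of that section is the only text that names tests. For numerical data: "Comparisons of numerical variables are conducted with the Student’s *t* test or Mann–Whitney’ *U* test as appropriate". For the rest: "categorical variables and outcomes were compared by using the chi-squared test or Fisher exact test". It closes with a single rule: "Two-tailed *p* < 0.05 will be considered statistically significant". No test is assigned to the primary endpoint by name, and no unit of analysis is stated.

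**The concern.** An incidence that is sized in struts reads naturally as a categorical outcome counted over struts, so the listed test that fits is a strut-level chi-squared or Fisher test. Struts in one patient share an operator, a lesion and a healing response. The Introduction itself names embedment, apposition and plaque composition as determinants of coverage, and these vary between lesions and patients more than between neighbouring struts. Zero within-patient correlation is therefore implausible. If struts are analysed as independent, standard errors are too small and superiority or non-inferiority can be declared by chance far more often than planned. Pooling also gives more weight to patients with more stent, and Table 1 allows up to three stents per patient.

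A second mismatch concerns the hypotheses. The listed tests compare groups against a difference of zero at two-tailed 0.05. None refers to the 1.3-point margin of hypothesis 2, and the level differs from the one-sided 0.05 set for hypothesis 3. The trial is meant to inform earlier stopping of DAPT, so a false positive would matter.

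**Working it through.** **1. Inputs (Statistical considerations and Table 4).** Coverage 93.6% vs 92% (hypothesis 1), 95% vs 95% with margin 1.3% (hypothesis 2), 96.5% vs 95% (hypothesis 3); one-sided levels 0.025, 0.025, 0.05; power 95%; 24 mm of stent, 0.4 mm spacing, 7.9 struts per cross-section; 16 evaluable patients per group.

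**2. Reproducing the plan's figures, struts taken as independent.**

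- Hypotheses 1 and 3: n = [z(1-α)·√(2p̄q̄) + z(0.95)·√(p₁q₁ + p₂q₂)]² / (p₁ - p₂)².
  - Hypothesis 1: (1.960 × 0.36556 + 1.645 × 0.36538)² / 0.016² = 6,781.
  - Hypothesis 3: (1.645 × 0.28529 + 1.645 × 0.28509)² / 0.015² = 3,912.
- Hypothesis 2: (1.960 + 1.645)² × (2 × 0.95 × 0.05) / 0.013² = 7,305.
- Struts per patient: 24/0.4 × 7.9 = 474. Patients: 7,305/474 = 15.4, so 16; 16/0.8 = 20.

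All figures match exactly, with no design effect. The plan therefore counts every strut as an independent unit.

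**3. Effect of clustering on a strut-level test.** The ICC is an assumption. Design effect D = 1 + (474 - 1) × ICC. Standard errors are too small by √D. True one-sided size = 1 - Φ(z/√D), with z = 1.960 for hypotheses 1 and 2 and z = 1.645 for hypothesis 3. Power uses the effective sample 16 × 474 / D per group and a normal approximation.

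| ICC | D | √D | True size, H1/H2 (nominal 2.5%) | True size, H3 (nominal 5%) | Power H1 | Power H2 | Evaluable patients per group for H2 at 95% power |
|---|---|---|---|---|---|---|---|
| 0.005 | 3.4 | 1.8 | 14% | 18% | 55% | 52% | 52 |
| 0.01 | 5.7 | 2.4 | 21% | 25% | 36% | 34% | 89 |
| 0.02 | 10.5 | 3.2 | 27% | 31% | 22% | 21% | 162 |
| 0.05 | 24.7 | 5.0 | 35% | 37% | 12% | 11% | 380 |
| 0.10 | 48.3 | 7.0 | 39% | 41% | 8% | 8% | 745 |

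The power columns refer to an analysis that respects clustering. Example for the last column: 7,305 × 3.365 / 474 = 51.9, so 52.

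**4. Simulation check.** Beta-binomial data, 16 patients × 474 struts per group, 20,000 runs at each ICC of 0.01, 0.02, 0.05 and 0.10:

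- Strut-level test, no true difference: falsely favourable in 20%, 27%, 35% and 39% of runs (nominal 2.5%).
- Strut-level non-inferiority test, true deficit of exactly 1.3 points: wrongly passed in 21%, 27%, 34% and 39% (nominal 2.5%).
- t-test on one percentage per patient, no true difference: rejected in 4.5% to 5.1% (nominal two-sided 5%).

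**5. The listed tests against the three hypotheses.**

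- Hypothesis 1: two-tailed 0.05, read in the favourable direction, equals one-sided 0.025. The two statements can be reconciled.
- Hypothesis 2: a test of zero difference does not address a margin. In the same simulation, with a true deficit of 1.3 points, a two-tailed patient-level t-test was non-significant in 71% to 92% of runs, so non-significance would be no evidence of non-inferiority.
- Hypothesis 3: one-sided 0.05 and two-tailed 0.05 are different criteria. The section gives both.

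**The case against.** The strongest reply is that the paragraph on tests is generic and never assigns chi-squared to the primary endpoint. Table 3's wording allows coverage to be a numerical variable, and the Discussion cites another trial's coverage as mean ± SD. One percentage per patient, compared by t or Mann-Whitney, is within the listed methods and respects clustering. This stands. A reader might infer that every listed test ignores clustering; the article does not support that. What remains is that it does not fix the patient as the unit, while its sample size fixes the strut.

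A reader might also infer that non-inferiority is not really planned, or that a non-significant difference would be taken as success. Neither is supported: hypothesis 2 is labelled non-inferiority, has a margin and a one-sided level, and its strut count comes from a non-inferiority formula. An analysis plan that is not shown may hold the procedure. The absence of that detail would not be a point by itself. The point is that the published test paragraph gives one two-tailed rule that does not fit the hypotheses set out just before it.

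Finally, the size of the error depends on an ICC that the article does not give. That also stands, and the result is therefore a range.

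**Conclusion.** The concern holds in conditional form. If the primary comparisons are run on the unit for which the trial is sized, with the listed test that matches it, the true one-sided error is about 14% to 39% for hypotheses 1 and 2 (nominal 2.5%) and about 18% to 41% for hypothesis 3 (nominal 5%). Standard errors are too small by a factor of about 1.8 to 7. These figures assume an ICC of 0.005 to 0.10, 474 struts in every patient and 16 evaluable patients per arm. Even the lowest ICC in the range gives more than five times the nominal 2.5%.

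It would go too far to say that the trial will produce false claims. A patient-level analysis is open under the text and keeps its error rate; its weakness is power. On either reading the section needs correction: the strut-level route is invalid, and the patient-level route does not deliver the stated 95% power. The mismatch between the two-tailed rule and the stated hypotheses is real for hypotheses 2 and 3 and only one of form for hypothesis 1.

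**What to change.** 1. **Unit.** State that the primary comparisons use the patient: one coverage percentage per patient (covered over analysable struts across the study stents), compared by t-test or linear model. Alternatively, use a GEE or mixed model on struts clustered by patient, with a small-sample correction. Report strut-pooled percentages only descriptively. Centre as a covariate is optional.
2. **Decision rules.** Hypothesis 1: two-sided 95% confidence interval for O3 minus A3 against 0. Hypothesis 2: lower limit of the two-sided 95% interval for O3 minus A6 against -1.3 points. Hypothesis 3: interval for O3 minus A6 against 0, at the level that Statistical considerations assigns to it.
3. **Levels.** Limit the two-tailed 0.05 rule to the other comparisons.
4. **Power.** Restate it with an assumed ICC and a range.

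**Cost.** Steps 1 to 3 change wording and analysis, not conduct. Intervals widen, and a mean of patient percentages weights patients equally, so it can differ somewhat from the pooled strut percentage. The main cost is candour on power: with 16 evaluable patients per arm it falls from the stated 95% to about 55% to 8% for hypothesis 1 and 52% to 8% for hypothesis 2. Restoring 95% for hypothesis 2 would take about 52 to 745 evaluable patients per group over the same ICC range. If the trial stays at 20 per group, the article should say that it cannot support firm conclusions on these hypotheses at the stated power.
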